**Fig. 2 Fig2:**
[figure not shown]
Overview of Study Components

**Table 3 Tab3:** Bi-Weekly videoconferencing topics for the supervised physical activity group plus behavioral counseling (PA + BC; intervention group) and supervised physical activity group plus exercise counseling (PA + EC; attention control group)

Week& Format	Description of Behavioral Strategies (PA + BC group)	Multi-process Action Control (M-PAC) Constructs for PA + BC Group Mapped to Behavior Change TechniquesUsed in Michie et al. (2013)^a^	Topics for Attention Control Group (PA + EC group)
2 Group	*Target M-PAC construct: Reflective processes (instrumental/affective attitudes)* Discuss the benefits of increasing physical activity for health and clinical outcomes, and how to make activity enjoyable	5.1 Information about health consequences 5.2 Salience of consequences 5.3 Information about social and environmental consequences 3.3 Social support (emotional) 5.6 Information about emotional consequences 7.5 Remove aversive stimulus 12.5 Adding objects to the environment	Physical activity guidelines
4 1:1	*Target M-PAC construct: Regulatory processes (goal setting)* Setting challenging, yet achievable goals using the SMART goal guidelines and developing rewards for achieving goals	11.1 Goal setting (behavior) 1.2 Problem solving 1.3 Goal setting (outcome) 1.8 Behavioral contract 2.3 Self-monitoring of behavior 2.6 Biofeedback 7.1 Prompt/cues 10.7 Self-incentive 11.2 Reduce negative emotions 13.4 Valued self-identity	Components of a physical activity training session
6 1:1	*Target M-PAC construct: Regulatory processes (action planning)* Action planning will be targeted by creating plans for increasing physical activity	1.1 Goal setting (behavior) 1.2 Problem solving 1.8 Behavioral contract 2.3 Self-monitoring of behavior 2.6 Biofeedback 7.1 Prompt/cues 10.7 Self-incentive 11.2. Reduce negative emotions	Physical activity intensity (e.g., heart rate training)
8 Group	*Target M-PAC construct: Regulatory processes* (self-monitoring) Discussion of how to monitor physical activity using wearables (e.g., Fitbits) and logs to keep track of progress towards goals	1.1 Goal setting (behavior) 1.2 Problem solving 1.4 Action planning 1.8 Behavioral contract 2.3 Self-monitoring of behavior 2.6 Biofeedback 7.1 Prompt/cues 10.7 Self-incentive 11.2 Reduce negative emotions 15.4 Self-talk	Signs and symptoms for stopping physical activity
10 Group	*Target M-PAC construct: Regulatory processes (coping planning*,* emotion regulation)* Discussing common psychologic, emotional, and environmental barriers to physical activity and strategies to overcome them	1.1 Goal setting (behavior) 1.2 Problem solving 1.4 Action planning 1.8 Behavioral contract 2.3 Self-monitoring of behavior 2.6 Biofeedback 7.1 Prompt/cues 10.7 Self-incentive 11.2 Reduce negative emotions 15.4 Self-talk	Stretching routine
12 1:1	*Target M-PAC construct: Regulatory processes (social support)* Discussion of social support and how to obtain support from significant others (i.e., spouse, friend, siblings)	3.2 Social support (practical) 12.1 Restructuring the physical environment 12.2 Restructuring the social environment	How to progress safely through a physical activity program
14 Group	*Target M-PAC construct: Reflexive processes (habit)* Identifying environmental cues to increase physical activity such as cues paired with time of the day, place, event, or other habits	7.1 Prompt/cues 7.5 Remove aversive stimulus 7.8 Associative learning 8.1 Behavioral practice 8.3 Habit formation	What to wear during physical activity
16 1:1	*Target M-PAC construct: Reflexive processes (habit)* Reinforcing a physical activity routine based on tagging physical activity to existing schedule and reminders strategies to reinforce the cues	7.1 Prompt/cues 7.5 Remove aversive stimulus 7.8 Associative learning 8.1 Behavioral practice 8.3 Habit formation	Importance of hydration
18 Group	*Target M-PAC construct: Reflexive processes (identity)* Building a physical activity identity by brainstorming and prioritizing various identities and where physical activity fits in	6.2 Social comparison 8.1 Behavioral practice 8.2 Behavioral substitution 12.5 Adding objects to the environment 13.2 Framing/reframing 13.3 Incompatible beliefs 13.4 Valued self-identity 13.5 Identity associated with changed behavior	Cross training
20 1:1	*Target M-PAC construct: Reflexive processes (identity)* Continue building a physical activity identity by prioritizing physical activity and finding personal meaning in participating in physical activity	6.2 Social comparison 8.1 Behavioral practice 8.2 Behavioral substitution 12.5 Adding objects to the environment 13.2 Framing/reframing 13.3 Incompatible beliefs 13.4 Valued self-identity 13.5 Identity associated with changed behavior	Feedback for progress to date
22 Group	*Booster session* Participants are free to raise any challenges and barriers to their activity goals or to revisit previous topics discussed	Behavior change techniques will depend on session revisited	Feedback for progress to date or revisit one of the earlier topics discussed
24 1:1	*Booster session* Participants are free to raise any challenges and barriers to their activity goals or to revisit previous topics discussed	Behavior change techniques will depend on session revisited	Feedback for progress to date or revisit one of the earlier topics discussed

### Data collection

All primary and secondary outcomes will be measured at baseline (T0), midpoint (i.e., 3 months into intervention; T1), T2 (i.e., immediately post-intervention [6 months]), T3 (i.e., 6-month follow-up from post-intervention), and T4 (i.e., 1-year follow-up from post-intervention).

#### Primary outcome

*Moderate-to-Vigorous Intensity Physical Activity* - Changes in MVPA will be assessed by accelerometry (ActiGraph Inc., Pensacola, FL.; model GT3X +). [56]Participants will be mailed an accelerometer to wear on their right hip, fastened to a belt worn around the waist. The accelerometer will be worn during waking hours for 7 days, except when bathing or swimming and returned to study staff via a postage-paid envelope. Activity data will be collected in one-minute intervals (epochs), with the total number of counts for each day summed and divided by the number of days of monitoring to arrive at an average number of activity counts. Cut-points will be based on Freedson et al. [56](i.e., 100–1,951 counts•minute − 1 for light PA; ≥1952 counts•minute − 1 for MVPA). The ActiLife© software will be used for processing and analysis of the data. The device is accurate for predicting energy expenditure (and time spent in PA) for walking (2–5 mph) and running on a flat surface (~ 5.6 mph; 0% slope [57]. The participant will also be mailed the accelerometer wear time log and the instructions to ensure the devices are worn properly and wear time is tracked.

#### Secondary outcomes

*Self-reported Physical Activity -* PA will be measured using a modified version of the (GLTEQ) Godin-Leisure Time Exercise Questionnaire [45] This measure asks participants to self-report the frequency and duration of light, moderate, vigorous intensity aerobic PA and resistance training for a typical week. This measure exhibits good reliability with coefficients of 0.83 and 0.85 [45]. 

*Reflective*,* Regulatory*,* and Reflexive Processes -* Standard measures from the M-PAC framework will be assessed including reflective processes of attitudes, and perceived capability and opportunity on a 7-point bipolar Likert scale [30, 31]. These items have been used with people LWBC [31, 32, 58]. Regulatory processes will be assessed with six items examining action and coping planning for PA using a 7-point scale (i.e., no plans–detailed plans) [59] Additionally, the Physical Activity Regulation Scale [59] be used as an additional measure of regulatory processes. The 14-item questionnaire measures proactive and reactive regulation, social monitoring, and self-monitoring and has displayed good internal consistency (> 0.80) [59]. Reflexive processes will be measured with the self-reported automaticity subscale that characterizes habit by automatic activation, behavioral frequency, and relevance to self-identity [60], and the exercise identity scale [61, 62] Cronbach’s alpha of these measures in previous studies in cancer range from 0.77 to 0.97 [62]. The M-PAC constructs have been validated and reliable based on years of prior research (see Table 3 in Rhodes et al., 2017 [30]paper).

*Physical Function -* Select measures from the Senior Fitness Test [63] will be used to assess physical function remotely: 30-s chair stand test for lower body strength and the 6-minute walk test for aerobic endurance. Higher scores or distance walked indicates better physical function across the domains.

*Quality of Life -* QoL will be assessed by the validated Functional Assessment of Cancer Therapy-General (FACT-G) which consists of physical well-being (PWB), functional well-being (FWB), emotional well-being (EWB), and social well-being (SWB) [64]. The FACT-Fatigue (FACT-F) scale includes the 27 items from the FACT-G scale plus the 13-item fatigue subscale, which is our primary QoL outcomes [64, 65]. Test-retest reliability is 0.92 for the total scale and 0.82–0.88 for subscales [64]. QoL will also be assessed with the EuroQol-5D (Eq. 5D) [66] as a part of the evaluation of cost-effectiveness.

*Demographic*,* Gender*,* Medical Information and Participant Satisfaction -* Demographic variables include: age, sex, gender, marital status, highest level of education, current employment status, ethnicity, PA history, and body mass index. Medical variables include: cancer type, time since diagnosis, disease stage, current/prior treatments, previous recurrence, current disease status, and comorbidities [67, 72]. Participant satisfaction items will assess burden and overall impressions similar to our prior work in people LWBC [32, 49]. We will disaggregate and analyze all primary and secondary outcomes by gender and sex [68]. 

Other demographic (e.g., age, ethnicity) and clinical (e.g., time since treatment) variables that intersect with gender will also be considered. The approach recommended by experts in gender-related measures is the two-step approach (Centre of Excellence for Transgender Health), which involves asking participants about both their current gender identity and their sex assigned at birth [69]. The Gender Index [70–72] will be used which includes all four aspects of gender (e.g., gender roles, gender relations, institutionalized gender, gender identity). Specific M-PAC constructs (e.g., perceived capability, habit, identity) may vary by sex and gender, thus targeting these considerations may maximize the potential effectiveness of PA interventions [41, 73]. This will prompt gender-specific, patient-centric care pathways for PA interventions designed to maximize the effectiveness of PA and patient outcomes.

*Health Economics Evaluation -* Health Economics Evaluation-Costs will be tracked using the Health Service Utilization Inventory [74] and the iMTA Productivity Cost Questionnaire [75] to conduct cost-effectiveness analyses. The incremental cost of the intervention will be estimated and compared to changes in utility values converted from EQ5D results [76] to evaluate the incremental cost per quality-adjusted life year (QALY) of the PA + BC group. This study will be conducted from the perspective of the Canadian public healthcare payer and the participant. This inventory will be partially completed by each participant as well as members of the research team. Participants will complete the Health-Service Utilization Inventory and the research team will complete the iMTA Productivity Cost Questionnaire.

#### Statistical analysis

A series of multilevel models using full information maximum likelihood to examine changes in the primary (i.e., MVPA) and secondary outcomes (i.e., reflective, regulatory, and reflexive processes from the M-PAC, physical function, QoL) will be conducted at the four time points. Multilevel modelling allows for simultaneous assessments of within person variations at each time measurement (level 1), which will be nested within study group (level 2). Finally, study group will be nested within study site (level 3). Although our primary time point of T2 will confirm the adherence reported post-intervention, inclusion of the T3 and T4 assessments allows us to determine if adherence is maintained. Fixed effects included in models will be time (i.e., baseline, T1, T2, T3, and T4), group (i.e., PA + BC intervention and PA + EC attention control), and interaction. All models will be estimated while adjusting for covariates (e.g., baseline PA, age, sex, treatment and cancer type). We will use the same analytical approach to assess differences across subgroups (e.g., sex, gender, drop-outs) by modeling the changes over time. Differences between men and women will be analyzed by adding a gender indicator variable to each of the models. The gender covariate will be crossed with the model’s independent variable so their interaction will be in the model. An intention-to-treat analysis will be used. For missing data at post-intervention or follow-up, all available data will be included under the missing-at-random assumption of the mixed-model analysis. Additionally, sensitivity analyses will be conducted to evaluate the robustness of our findings under alternative missing data assumptions, such as not-missing-at-random. The PROCESS macro for SPSS [77] will be used to examine mediation effects of the reflective, regulatory, and reflexive processes between groups (PA + BC group; PA + EC group) and MVPA and indirect effects across the path model. Cost and QALY differences between groups will be calculated using ordinary least squares regression analyses. Incremental cost-effectiveness ratios (ICER) will be calculated by dividing the adjusted incremental costs by incremental effects. ICER uncertainty will be measured by bootstrapping using at least 5000 replications.

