#### Randomization

Participants will be 1:1 randomized to either the PA + EC or the PA + BC group. Randomization will be performed using a stratified randomization scheme in the REDCap Randomization Module after baseline assessments. The sequence will be random permuted blocks of varying sizes, stratified by prior chemotherapy (yes versus no), age (< 65 versus ≥ 65 years), and sex (female versus male) to balance treatment characteristics that would potentially impact the severity of fatigue and intervention response [46]. Randomization codes will be kept in a pre-made digital file that is separate from other study records. Only the research co-ordinator will have access to the randomization codes. Following randomization, the research co-ordinator will update the randomization log to indicate the code has been used and include the ID number of the participant it was assigned to.

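### The stated multilevel hierarchy has no participant level and nests measurements in study group; followed as written, standard errors are too small for some contrasts and too large for others

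*Protocol article*

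**What the plan says.** The Statistical analysis section of the protocol article describes "A series of multilevel models using full information maximum likelihood" for the primary and secondary outcomes. It then lists the levels. Level 1 and level 2 are given as "within person variations at each time measurement (level 1), which will be nested within study group (level 2"). The list closes with "Finally, study group will be nested within study site (level 3"). No participant level, participant random effect or within-participant covariance is named.

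The same section also makes treatment a fixed effect. Its fixed terms are the five assessments from T0 to T4 and, as a further entry, "group (i.e., PA + BC intervention and PA + EC attention control), and interaction". It adjusts all models for covariates that include baseline PA, and it names T2 as the primary time point ("Although our primary time point of T2 will confirm the adherence reported post-intervention").

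The Randomization section says "Participants will be 1:1 randomized to either the PA + EC or the PA + BC group", with the allocation "stratified by prior chemotherapy (yes versus no), age (< 65 versus ≥ 65 years), and sex (female versus male"). Site is not named as a stratum, and nothing is allocated by site.

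**The concern.** Three features of the stated structure conflict with the design.

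- **The participant is missing.** Each person contributes up to five measurements, which are correlated. The person is also the unit randomized. The listed hierarchy has no place for that correlation.
- **Group appears twice.** It is a treatment with two categories, already a fixed effect. It is not a sample of clusters and cannot usefully be a random level as well.
- **Group is not nested in site.** Individuals are randomized and sites are not, so both groups can occur at any site. Group and site are crossed.

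An analyst who codes the sentences as they stand treats repeated measurements on one person as independent once group, site and covariates are accounted for. Comparisons between people averaged over visits then look too precise, and comparisons of change within people look too imprecise. The same models serve the secondary outcomes and the sex and gender interactions.

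**Working it through.** The plan gives no figure on this point to reproduce; the check is of what the stated structure does to standard errors.

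**Inputs.** From the documents: 196 analysed people, taken as 98 per group (Sample size); five visits, T0 to T4; alpha 0.05. Assumed: a two-sided test, complete data, equal variances scaled to 1, and one common within-person correlation ρ. The documents give neither ρ nor the number of sites. I use ρ = 0.4 to 0.7 unless stated.

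**Notation.** Let k = model SE / true SE. Type I error = 2[1 − Φ(1.96k)]. A test with 80% power under the correct SE has power 1 − Φ(1.96k − 2.80).

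**Step 1. No participant effect, no baseline covariate.**

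- Group effect averaged over T1 to T4: the true variance is 1 + 3ρ times the model's, so k = 1/√(1 + 3ρ). At ρ = 0.4 the factor is 2.2 and the error 18.6%; at ρ = 0.7 it is 3.1 and 26.6%.
- Group contrast in T2 minus T0: k = 1/√(1 − ρ), which is 1.29 at ρ = 0.4 and 1.83 at ρ = 0.7. The formula gives an error of 1.1% down to 0.03%; simulation gave about 0.9% down to 0.1%.
- Group contrast at T2 alone: k = 1. Simulated error is about 5%.

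**Step 2. Add the stated adjustment for baseline PA, still with no participant effect.** The text keeps baseline as a time level and also adjusts for it. The pooled slope on baseline is then b = (1 + 4ρ)/5. At a later visit the residual variance is v = 1 − 2bρ + b², and the residual covariance between two later visits is c = ρ − 2bρ + b². The pooled model variance is s² = [(1 − b)² + 4v]/5.

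| Quantity | ρ = 0.4 | ρ = 0.7 |
|---|---|---|
| b | 0.52 | 0.76 |
| v | 0.8544 | 0.5136 |
| c | 0.2544 | 0.2136 |
| s² | 0.7296 | 0.4224 |
| T1 to T4 average: true/model variance (v + 3c)/s² | 2.22 | 2.73 |
| type I error | 18.8% | 23.6% |
| T2 alone: true/model variance v/s² | 1.17 | 1.22 |
| type I error | 7.0% | 7.5% |
| T2 minus T0: k = √[s²/(1 − ρ)] | 1.10 | 1.19 |
| type I error | 3.1% | 2.0% |
| power of a nominal 80% test | 74% | 68% |

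Simulation agrees: 18 to 23% for the average, 6.6 to 8% for T2 alone and 1.7 to 3.3% for the change contrast. With k rounded to 1.2 the lower power is 67%.

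If baseline is a covariate only and the outcomes are T1 to T4, the residual correlation is ρ/(1 + ρ). The variance factor 1 + 3ρ/(1 + ρ) is then 1.86 to 2.24. The averaged effect has an error of 15 to 19%, and T2 alone is at 4.5 to 5.4%.

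**Step 3. The literal three-level model, with a random group-within-site term fitted by maximum likelihood** (simulated; ρ = 0.3 to 0.7; average over all five visits; no baseline covariate; no true site effect). The averaged group effect has an error of about 14 to 22% with 2 sites, 14 to 18% with 3, 12 to 15% with 4 and 10 to 13% with 6. The T2 minus T0 contrast keeps k at about 1.18 to 1.83, with an error of at most 2%. The extra term offsets part of the understated SE but does not remove it.

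**Step 4. The remedy.** With a participant random intercept (ρ = 0.3 to 0.7), simulated error is 4.8 to 5.5% for the averaged effect and 4.7 to 5.2% for the change contrast.

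**The case against.** The strongest reply is that this is a slip of wording. The section speaks of within-person variation and of a mixed-model analysis under missing at random, which makes sense only if measurements are grouped by person. It never calls group random. Details of random effects and covariance normally belong in an SAP, which is not shown. This is a fair reading, and it is why the consequence is stated conditionally. It does not dispose of the point, because the article does not leave the hierarchy open: it gives a closed list of three levels, and that list is wrong.

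The second reply is that T2 is the named primary time point and a comparison at T2 alone is nearly unaffected. That stands. However, the Sample size section powers a global treatment effect, the primary outcome is described as change in MVPA, and the model contains a group-by-time interaction. The averaged and change contrasts are therefore within the plan's scope.

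Stronger readings are tempting, and the documents do not support them:

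- A reader might infer that the SE for change is inflated 1.4-fold and that 80% power falls to 51%. Those are the ρ = 0.5 figures without baseline adjustment, and the plan adjusts for baseline PA.
- A reader might infer that the treatment test would rest on the number of sites, with a critical t of 4.30. That needs three sites and a small-sample reference with 2 degrees of freedom. The number of sites is not stated and the plan specifies maximum likelihood, under which the averaged test errs in the opposite direction (Step 3).

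The choices between fixed and random site, and between a random intercept and an unstructured covariance, are legitimately the SAP's.

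**Conclusion.** The stated hierarchy is wrong and contradicts the individual randomization and the plan's own list of fixed effects. The harm arises only if it is followed without a participant effect, and it then depends on the contrast:

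- **Averaged over T1 to T4:** too many false positives, about 19 to 27%, or about 18 to 23% with the stated baseline adjustment.
- **Change from T0 to T2:** conservative. Error is about 0.1 to 0.9% unadjusted. With baseline adjusted it is about 2 to 3%, with the SE overstated roughly 1.1 to 1.2-fold and 80% power reduced to about 67 to 74%.
- **T2 alone:** about 5%, rising to about 7 to 8% if baseline is both covariate and time level.

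These sizes assume ρ of 0.4 to 0.7, a common correlation across visits, 196 people and complete data. The directions do not depend on the exact ρ, provided it is positive. It does not follow that the T2 comparison is invalid.

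**What to change.** Restate the hierarchy as visits (level 1) within participants (level 2), with a participant random effect or a within-participant covariance structure across visits. Keep group, time and group-by-time as fixed effects only. Handle site as a fixed covariate or as a level above participant. Delete the statements that nest measurements in group and group in site. While rewriting, say whether baseline MVPA is a covariate or a time level, since using it as both shifts the T2 contrast slightly. The cost is a change of wording in the protocol and SAP; design, data collection and sample size are untouched.

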**Methods:**

This study is a two-armed, multi-site randomized controlled trial (RCT). People LWBC will be recruited and randomized to a 6-month virtual supervised PA intervention plus standard exercise counseling (PA + EC group; *n* = 118) or a 6-month virtual supervised PA plus behavioral counseling based on the Multi-Process Action Control (M-PAC) framework (PA + BC group; *n* = 118). Supervised PA will be delivered via synchronous Zoom classes that tapers to a home-based protocol at the end of the study. The goal of both groups is to gradually increase PA to the cancer PA guidelines (e.g., 90 min of MVPA/week). The PA + BC group will receive twelve behavioral counseling sessions with a qualified exercise professional (QEP), and the corresponding counseling session will be delivered bi-weekly. The behavioral counseling sessions will be based on the M-PAC’s reflective, regulatory, and reflexive processes. In addition to the supervised PA classes, the PA + EC (i.e., attention control group) will receive twelve standard PA counseling sessions based on PA training principles. People LWBC will complete measures at baseline, midpoint, post-intervention (6-months), at 6-months follow-up, and 1-year follow-up. Self-reported measures include quality of life (QoL), motivational outcomes, health economics, and patient satisfaction. Objective measures include PA via accelerometry. Multilevel modelling will examine change in the primary (i.e., PA) and secondary outcomes (i.e., motivational outcomes from the M-PAC, physical function, QoL) at the five time points.

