**Measures**						
**Primary outcome**						
Physical activity (ActiGraph accelerometers)	Worn for 7 days during waking hours only	X	X	X	X	X

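### The primary MVPA model uses baseline activity both as an outcome level and as a covariate, and the number of time points does not agree

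*Protocol article*

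**What the plan says.** All of this is in the protocol article.

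- **Outcome levels** (Statistical analysis): "Fixed effects included in models will be time (i.e., baseline, T1, T2, T3, and T4", together with "group (i.e., PA + BC intervention and PA + EC attention control), and interaction". Time has five levels, one of which is baseline.
- **Covariates** (same section, next sentence): "All models will be estimated while adjusting for covariates (e.g., baseline PA, age, sex, treatment and cancer type".
- **Number of time points.** The section opens by saying that the models "will be conducted at the four time points". The abstract says "at the five time points", and Data collection agrees with five: "All primary and secondary outcomes will be measured at baseline (T0), midpoint", followed by T2, T3 and T4.
- **What PA means.** The abstract gives PA as the primary outcome, and Table 1 lists that outcome as "Physical activity (ActiGraph accelerometers", measured at all five visits.
- **Primary time point** (Statistical analysis): "Although our primary time point of T2". The section does not say whether the T2 effect is the interaction contrast against baseline or the covariate-adjusted group difference at T2.

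**The concern.** Two coherent models are available. One takes T1 to T4 as outcomes with baseline as a covariate. The other takes T0 to T4 as outcomes without that covariate. The section combines them: four time points and a baseline covariate belong to the first, and a five-level time factor belongs to the second.

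With both features in the MVPA model, the response in each T0 row equals the covariate. Those rows carry no information on how baseline predicts later activity, yet they help to set the slope and the variance components. At stake is the primary outcome at its primary time point: either the adjustment achieves nothing, or the T2 standard error is too small.

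**Working it through.** **Inputs.** From the documents: five outcome times, two arms randomized 1:1, group-by-time interaction, baseline PA as a covariate, and N = 196 for 80% power at alpha 0.05 (Sample size section). Assumed, because the article gives neither: a correlation rho between visits, and a participant random intercept. Total variance is set to 1.

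**The plan's own figure.** No SD is stated, so 196 cannot be rebuilt from the article alone. It fits a standardised difference d of 0.40, which for 24 min per day implies an SD of 24/0.40 = 60. With 98 per arm, 0.40 × √(98/2) = 2.80, and Φ(2.80 − 1.96) = 80%. This reconstruction uses no baseline adjustment.

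**Reading A: T2 effect as group-by-time (T2 minus T0).** A covariate that is constant over time, with one common slope, cancels from a within-person contrast. In simulation without dropout, the estimate and SE were identical with and without the covariate. With 20% dropout they were nearly so (SE 0.1457 against 0.1474 at rho 0.5). What remains is a change-score difference:

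- change-score variance: 2(1 − rho)
- ANCOVA variance (T2 adjusted for baseline): 1 − rho²
- ratio: 2(1 − rho)/(1 − rho²) = 2/(1 + rho)

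This is 2/1.4 = 1.43 at rho 0.4, 2/1.5 = 1.33 at 0.5 and 2/1.7 = 1.18 at 0.7.

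**Reading B: T2 effect as the adjusted group difference at T2.** With five balanced occasions:

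- fitted slope: b = (1 + 4rho)/5, instead of rho
- true variance of the adjusted T2 value: 1 + b² − 2b·rho
- variance the model reports: (1 − rho) + [b(1 − b) − (1 − rho)/5]

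At rho 0.5, b = 3/5 = 0.60. The true variance is 1 + 0.36 − 0.60 = 0.76. The model variance is 0.50 + (0.24 − 0.10) = 0.64. The SE ratio is √(0.64/0.76) = 0.918, and the type I error is 2Φ(−1.96 × 0.918) = 7.2%.

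| rho | slope b | model var | true var | SE too small by | type I error |
|---|---|---|---|---|---|
| 0.3 | 0.44 | 0.806 | 0.930 | 7% | 6.8% |
| 0.5 | 0.60 | 0.640 | 0.760 | 8% | 7.2% |
| 0.7 | 0.76 | 0.422 | 0.514 | 9% | 7.6% |

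**Simulation check of reading B** (no treatment effect, 98 per arm, 1500 runs per setting, random-intercept ML). With compound symmetry, rho 0.5 and no dropout, the mean model SE was 0.114 against an empirical SD of 0.124, and type I error was 7.5%. Twelve settings were run: compound symmetry or AR(1), rho 0.3, 0.5 or 0.7, and 0% or 20% dropout. The SE was too small by about 5% to 9.5% in eleven of them and by 11% in one. Type I error ranged from 6.5% to 8.4%.

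**Baseline used once.** Simulated ANCOVA at T2 (compound symmetry, no dropout) gave type I error of 4.9%, 5.8% and 4.7% at rho 0.3, 0.5 and 0.7. This is nominal within simulation error (about 0.6 percentage points).

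**The case against.** **Baseline PA may be self-reported.** The outcome is called MVPA and the covariate PA, inside a list of examples. Self-reported PA is a separate secondary measure, and eligibility is screened on self-report. If the covariate were self-reported, the T0 response and the covariate would differ and the exact duplication would go. This stands as a limit. But the abstract and Table 1 use PA for the accelerometer outcome, so the duplication is the more natural reading, and the term needs defining either way.

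**The likely contrast is benign.** The section speaks of change over time and lists an interaction, which points to reading A. That estimate is unbiased. This also stands: on reading A the cost is efficiency only.

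**Power.** A reader might infer that the trial falls short of its 80%. An effect with 80% power under ANCOVA would indeed have Φ(2.80/√1.43 − 1.96) = 65% as a change score at rho 0.4, and 73% at rho 0.7. But the article does not say that it was powered on ANCOVA. With d = 0.40 and 98 per arm, change-score power is 72%, 80% and 95% at rho 0.4, 0.5 and 0.7, against 86%, 90% and 97% for ANCOVA. Whether it falls below 80% depends on an SD and a correlation that the article does not state. Only the forgone gain can be shown.

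**The analysis plan may settle it.** The covariance structure and the named contrast are commonly left there, and their absence is not the point. The point is that the published paragraph contradicts itself. A misspecified covariance can also inflate error by itself: in some AR(1) settings the interaction reached 8.2% with or without the covariate. The inflation in reading B does not rest on that, because with compound symmetry, where the random intercept is the right structure, it was still 6.5% to 7.9%.

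**It may be a one-phrase slip.** Four time points with a baseline covariate is a sound model, so the error may lie only in the list of time levels. That makes the repair easy, but the text does not show which phrase is wrong.

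**Conclusion.** The point holds for the MVPA model, provided that baseline PA means accelerometer activity. The two consequences are alternatives. On the interaction reading, the adjustment is wasted and the variance is 1.43 to 1.18 times that of ANCOVA for an assumed rho of 0.4 to 0.7, with no bias and nominal error if the covariance is right. On the adjusted-difference reading, under an assumed random intercept, the SE is about 5–9% too small and type I error is about 7%. Randomization protects the point estimate in both cases.

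A reader might also infer that every model in the series is affected. The documents do not support that: baseline PA is not the outcome's own baseline in the M-PAC, physical function and QoL models. The disagreement between four and five time points is certain from the text and needs no assumption. The plan should be changed, because the primary estimate depends on which reading is implemented.

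**What to change.** Use baseline MVPA once in the MVPA model, in one of two ways:

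1. Model T1 to T4 as outcomes, with baseline MVPA and baseline-by-time as covariates, and name the adjusted PA + BC minus PA + EC difference at T2 as the primary estimate.
2. Keep T0 as an outcome level, constrain the baseline means to be equal across arms, and drop baseline PA as a covariate in that model.

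Then make the number of time points agree with the choice throughout, and state that baseline PA means accelerometer MVPA.

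The cost is wording in the protocol and analysis plan. No new measurement is needed, because MVPA is already scheduled at T0 to T4.
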